## Methods

### Design and Study Population

This will be a randomized, double-blind, sham-controlled, 6-week clinical trial, comprising 5 consecutive days a week sessions for the first 3 weeks and then 2 days a week (interval at least 1 day between sessions) for a further 3 weeks of active or sham TBS. The study will be conducted at the Institute of Psychiatry of the School of Medicine of the University of Sao Paulo (HCFMUSP). The study will be conducted in accordance with the principles established by the Declaration of Helsinki (45) and the American Document of Good Clinical Practice (46). This protocol have been published in www.clinicaltrials.gov with the number NCT04123301.

Ninety adult patients aged 18 to 65 years with a diagnosis of type I BD, type II BD or MDD in moderate or severe depressive episode (according to DSM-5 criteria) with mixed features (according to DSM-5 criteria plus symptoms of distractibility, irritability and psychomotor agitation). The diagnosis will be confirmed by the Portuguese version of the structured interview of DSM-IV (Structured Clinical Interview—SCID IV) (47) modified with the DSM-5 criteria and specifiers without the exclusion of symptoms distractibility, irritability, and psychomotor agitation, since there isn't a Portuguese version of the SCID of DSM-5. Recruitment strategies will include referrals from other doctors and advertising at internet and newspapers. Participants will be randomized using a computer generated list for one of two intervention groups (in a 1:1 ratio) to the active or sham TBS group. Allocation masking will be done by sequentially numbered cards that will determine which group each patient belongs to. The card determines whether the coil to be used will produce active or sham stimulation. A person not directly involved in the clinical trial will be responsible for delivering the sham or true coil according to randomization, remembering that the coils are physically identical and have similar sound properties and stimuli. Participants and staff will be unaware of the status of allocation groups.

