### Inclusion and Exclusion Criteria

Eligibility criteria is the presence of manic polarity symptoms during a moderate or severe depressive episode of BD I, BD II or MDD. We set the Montgomery–Åsberg Depression Rating Scale (MADRS) (48) with a score between 20 and 34 points for the definition of moderate major depressive episode and above 34 points for severe major depressive episode. The definition of major depressive episode with mixed features will be performed using the Young Mania Rating Scale (YMRS) (49) with ≥1 point on three or more items according to criteria used in the International Mood Disorders Collaborative Project (12) and consist with other definitions of depression with mixed features (50–53). Patients will be included in any appropriate pharmacological regimen (first or second line) according to the Canadian Network for Mood and Anxiety Treatments (CANMAT) guidelines to treat a major depressive episode of MDD or BD (I or II) (54, 55) and still have mixed depressive symptoms, so that TBS will be applied as an add-on treatment. We will not make adjustments to patient treatments, we will only enroll patients that are already on a stable psychopharmacological regimen (at least one month) of first or second line according to CANMAT but with no response/remission or partial response (still meeting inclusion criteria). The pharmacological regimen should be maintained on the same schedule and dosage from the beginning to the end of the study and patients will not be in a psychotherapy regimen. Drugs such as benzodiazepines will only be allowed at low doses (less than 3 mg per day of lorazepam or equivalent). Exclusion criteria will be: concomitant diagnosis of other neuropsychiatric disorders such as: schizophrenia, dementias, mental retardation, organic mental disorder, or epilepsy; psychotic depression; acute suicide ideation (assessed by interview and clinical evaluation); suspected or confirmed pregnancy; women in breastfeeding; severe or unstable clinical disease; specific contraindications to TBS (previous epileptic seizures; change in electroencephalogram at some point in life; previous stroke; previous severe TBI (with neurosurgery); metallic object on head (except mouth) as projectile piece, surgical clip, welding fragments; any implanted device (cardiac pacemaker, intravenous catheter). Personality, anxiety, and substance use disorders will be allowed as comorbidity provided the primary diagnosis is BD or MDD.

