Clinical assessments will be conducted weekly until the end of week 3 and thereafter a final assessment will be conducted at the end of week 6. Adverse events will be evaluated every day during the first week and then once a week until the end of the week 6. The neuropsychological assessment battery will be applied before the patient is stimulated and at the end of the week 6 of intervention (**Table 2**).

**Table 2 T2:** Measurement outcomes over time.

Scales	Baseline	End of week 1	End of week 2	End of week 3	End of week 6
SCID I/P modified	X				
MADRS	X	X	X	X	X
YMRS	X	X	X	X	X
*WHOQOL-bref*	X	X	X	X	X
BIS-11	X	X	X	X	X
CGI-S	X	X	X	X	X
GAF	X	X	X	X	X
HAM-A	X	X	X	X	X
BRIAN	X	X	X	X	X
Morningness–Eveningness Questionnaire	X				
TMS' Typical side Effects Scale	X	X	X	X	X
UKU-SERS	X	X	X	X	X
Neuropsychological Assessment	X				X

SCID, Structured Clinical Interview; MADRS, Montgomery–Åsberg Depression Scale; YMRS, Young Mania Rating Scale; WHOQOL, World Health Organization questionnaire; BIS-11, Barratt Impulsivity Scale; GAF, Global Assessment of Functioning; HAM-A, Hamilton Anxiety Scale; BRIAN, Biological Rhythm Interview of Assessment in Neuropsychiatry; TMS, transcranial magnetic stimulation; UKU-SERS, Udvalg for Kliniske Undersøgelser Side Effect Rating Scale; CGI-S, Clinical global impression - Severity.

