Primary outcome will be change in MADRS from baseline to week 3. Secondary outcomes will be: change in YMRS at the end of week 3 and 6 of treatment; response rates (50% or more of reduction in MADRS at the end of weeks 3 and 6 of treatment); remission rates (MADRS <11 (56) at the end of weeks 3 and 6 of treatment); change in anxious symptoms assessed by Hamilton Anxiety Scale (HAM-A) (57) at the end of weeks 3 and 6 of treatment; change in overall clinical impression assessed by Global Clinical Impression of Severity (GCI-S) (58) and Global Assessment of Functioning (GAF) (59) at the end of weeks 3 and 6 of treatment; change of functionality assessed by abbreviated version of the World Health Organization questionnaire (WHOQOL) (60) at the end of weeks 3 and 6 of treatment; change of biological rhythms assessed by the Biological Rhythm Interview of Assessment in Neuropsychiatry (BRIAN) (61) at the end of weeks 3 and 6 of treatment; change of impulsivity assessed by Barratt Impulsivity Scale (BIS-11) (62) at the end of weeks 3 and 6 of treatment; association between the chronotype assessed by Morningness–Eveningness Questionnaire (63) and the severity of mixed depression assessed by MADRS; and change in neuropsychological battery parameters before and at the end of the intervention (6 weeks).

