### Statistical Analysis

Statistical analyses will be performed using Stata^®^ (67) and the Statistical Package for the Social Sciences—SPSS^®^ (68). The overall significance level for this study will be 0.05 using two-tailed tests. The study results will be analyzed for two patient populations: the intention-to-treat (ITT(and the per-protocol (PP) analysis set. The ITT set will include all subjects who met the study eligibility criteria and received at least one week active/sham TBS treatment. The PP population thus will include all subjects from the ITT set who receive the protocol-specified treatment and complete the 6-week treatment regimen or withdrew before completion per the study protocol. Comparisons of baseline demographic and clinical characteristics and safety assessments will be performed on the ITT analysis set. The primary efficacy analysis will be performed using the PP analysis set.

Comparisons of baseline demographic and clinical characteristics between the study groups will be performed to ensure that the groups are balanced at baseline and that the randomization is successful. For comparison of means (continuous variables), the two-sample t-test or a nonparametric equivalent will be used. For comparison of proportions (categorical variables), the chi-square test or Fisher's exact test will be used, as appropriate. The change in MADRS total score from baseline to week 3 (primary endpoint) will be compared between the treatment groups using a linear mixed model (69) with a continuous dependent variable (MADRS score) to measure the primary outcome. For primary outcome subject will be the random effect and the fixed factors will be intervention (sham × active). Secondary outcomes will also follow the same pattern and the scales' scores will be the random effect and the fixed factors will be intervention (sham × active). Since patients will be taking different medications and dosages, the defined daily dose (DDD) will be used in the statistical analysis. This enables the inclusion of several medications and doses in the model, as medication groups (e.g., antidepressants, anticonvulsants, etc.).

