### Reasons for Withdrawal or Termination

Patients will be withdrawn from the study if they meet one or more of the following criteria:

(1) Leave the study on their own accord;

(2) Two consecutive visits OR three or more non-consecutive visits;

(3) Have severe clinical or psychiatric events (at clinical assessment) during the study:.

These criteria will be analyzed on a case-by-case basis according to the clinical assessment that the psychiatrist may be considering. Examples of serious clinical events are: neurological deficits, cardiovascular deficits, endocrine decompensation, loss of consciousness, syncope; and others. Examples of serious psychiatric events are: suicidal ideation, suicide attempt, autoaggressiveness (self-mutilation), hetero-agressivity, severe anxiety, severe psychosis, etc.

(4) Serious adverse effects (at clinical assessment) during the study:

These criteria will be analyzed on a case-by-case basis according to the clinical assessment that the psychiatrist may be considering. Examples of serious adverse effects: severe or frequent headaches, severe cervical pain, severe scalp pain, severe scalp burning, severe dizziness, severe nausea, and seizures.

(5) Worsening of depressive (>25% on the MADRS) or manic (>50% on the YMRS) symptomatology at the end of each week of treatment.

Patients with worsening scores on depressive symptom scales (increase on MADRS scores greater than 25%) or manic symptoms (increase on YMRS scores greater than 50%) at the end of each intervention week (compared to the previous week).

Patients who discontinue the study will be referred to the psychiatrist who referred the study for appropriate follow-up and management of the disease.

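### Criterion 5 withdraws patients on a percentage rise alone, so a patient in remission (MADRS 6 to 8) or with a low YMRS must leave the study after a change of 2 or 3 points

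*Protocol article*

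**What the plan says.** The Reasons for Withdrawal or Termination section opens with a mandatory rule: "Patients will be withdrawn from the study if they meet one or more of the following criteria". Criterion 5 is a MADRS rise above 25% or a YMRS rise above 50%. For the YMRS the text reads "manic symptoms (increase on YMRS scores greater than 50%) at the end of each intervention week (compared to the previous week". Both limits are relative and both use the previous week as reference. The criterion has no point floor, no score level, no confirmation visit and no exemption for remission.

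Clinical discretion is written elsewhere in that section: "These criteria will be analyzed on a case-by-case basis according to the clinical assessment that the psychiatrist may be considering". This sentence appears under criterion 3 and again under criterion 4, but not under criterion 5.

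Other relevant text:
- Inclusion and Exclusion Criteria: mixed features require a YMRS of "≥1 point on three or more items"; MADRS at entry is 20 or more.
- Design and Study Population: mixed features are also required "according to DSM-5 criteria plus symptoms of distractibility, irritability and psychomotor agitation".
- Schedule paragraph under Inclusion and Exclusion Criteria: "Clinical assessments will be conducted weekly until the end of week 3 and thereafter a final assessment will be conducted"; that last visit falls in week 6.
- Measurement of Variables and Outcomes: "Primary outcome will be change in MADRS from baseline to week 3"; remission is MADRS below 11.
- Statistical Analysis: the per-protocol set, used for the primary efficacy analysis, includes patients who "complete the 6-week treatment regimen or withdrew before completion per the study protocol".

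**The concern.** A percentage rule becomes hypersensitive as the reference score falls. This trial has low reference scores in two places. The YMRS entry rule can be met with a total of 3, and a MADRS responder can fall to single figures. There, a change of 2 or 3 points is enough for mandatory withdrawal, although on its face it need not mean clinical worsening.

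The cost depends on timing. The plan has 5 × 3 + 2 × 3 = 21 sessions.
- Week 1 trigger: 21 − 5 = 16 sessions lost, with the week 3 MADRS and the week 6 outcomes.
- Week 2 trigger: 21 − 10 = 11 sessions lost, with the same outcomes.
- Week 3 trigger: 21 − 15 = 6 sessions and the week 6 outcomes lost; the primary score is already in hand.
- Week 6: treatment is over, and with no week 4 or 5 assessment the only earlier score to compare with is week 3.

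**Working it through.** The plan gives no figure to reproduce here. The check has an exact part and an assumption-based part.

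**Exact part.** For a previous score p, find the smallest whole-number rise r with r/p > 0.50 (YMRS) or r/p > 0.25 (MADRS).

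| Scale | Previous → triggering score | Rise |
|---|---|---|
| YMRS | 3 → 5 | 2 (66.7%) |
| YMRS | 4 → 7 | 3 (75%) |
| YMRS | 5 → 8 | 3 (60%) |
| YMRS | 6 → 10 | 4 (66.7%) |
| YMRS | 8 → 13 | 5 (62.5%) |
| YMRS | 10 → 16 | 6 (60%) |
| MADRS | 6 → 8 | 2 (33.3%) |
| MADRS | 20 → 26 | 6 (30%) |
| MADRS | 35 → 44 | 9 (25.7%) |

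YMRS 4 → 6 is exactly 50% and does not trigger. From YMRS 0 the ratio is undefined. MADRS moves that trigger entirely below 11 include 1 → 2, 2 → 3, 3 → 4, 4 → 6, 5 → 7, 6 → 8 and 7 → 9. From 8 the smallest trigger is 11, which is outside remission. At entry-level MADRS the rule needs 6 to 9 points, so the fault is confined to low scores.

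**Assumption-based part.** The protocol gives neither a YMRS distribution nor a rating error. Assume that each score is the true score plus normal error, rounded and cut off at 0, that visits are independent, and that baseline YMRS is at least 3. Enumerate all score combinations for baseline, week 1 and week 2. Results are for rating-error SD 1 / SD 2. The columns are the current rule; the >50% rule plus a 5-point minimum; and that same test made against either the previous week or baseline (in this last column a 5-point rise from 0 also counts).

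| True YMRS path | Current | Minimum only | Minimum, previous week or baseline |
|---|---|---|---|
| stable 4 (false triggers) | 20.7% / 35.5% | 0.1% / 5.1% | 0.1% / 7.2% |
| stable 15 (false triggers) | 0.0% / 3.3% | 0.0% / 3.3% | 0.0% / 4.4% |
| 3-7-11 (detection) | 98% / 89% | 55% / 63% | 99% / 86% |

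Under the current rule, false triggers are 8.1% / 33.5% at a stable YMRS of 6 and 0.5% / 14.9% at 10, so the excess fades as scores rise.

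For a stable remitted patient at true MADRS 6, the chance of a trigger at one weekly comparison is 15.0%, 30.2% and 33.5% for SD 1, 2 and 3. If no trigger applies below 11, it is under 0.1%, 1.1% and 5.5%.

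**Why the YMRS minimum cannot stand alone.** Take observed scores of 3, 7, 11 and 16. The weekly rises are 4 points, 4 points, then 5/11 = 45%. None meets both conditions, so a fivefold rise never triggers. The current rule stops it at week 1 (4/3 = 133%). With the baseline test it stops at week 2: 11 − 3 = 8 points, or 267%.

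**The case against.** The strongest case is safety. The protocol states that TBS has not been trialled in mixed depressive episodes, and one side receives excitatory stimulation. A sensitive stopping rule that accepts some needless withdrawals is a defensible choice. Criterion 5 is the only criterion that names manic worsening; criterion 3 is limited to severe events and its examples do not include it. The 5-point figure has no source in the document. This stands, and it is why the YMRS minimum is not recommended alone. It does not defend withdrawing a remitted patient for MADRS 6 to 8.

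The MADRS case is also rarer than the YMRS case. From an entry score of at least 20, reaching 6 is a fall of at least (20 − 6)/20 = 70%, against a mean 52.5% reduction in the active arm of the trial used for the sample size. To cost the week 3 score, it must happen by week 1 and reverse by week 2. This stands too: the MADRS fault mostly affects treatment and outcomes after week 3.

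A reader might infer more than the document supports:
- *Withdrawn patients leave the primary analysis.* They do not. The per-protocol set keeps those withdrawn under the protocol, so their earlier scores can still enter the mixed model.
- *The arms are biased.* The rule applies equally to both, and nothing in the document shows a differential effect.
- *A fifth to a third of patients will be lost, exceeding the 10% dropout allowance.* Those rates are conditional on a true YMRS of 4 and an assumed error. A total of 3 is only the arithmetic floor, and the added diagnostic requirement may place most patients higher.

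In the other direction, one might extend the case-by-case sentence to criterion 5. The authors wrote it twice, each time under another criterion, so that is inference.

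**Conclusion.** The point holds as a flaw in how criterion 5 is fixed. That remitted patients and patients with low YMRS scores must be withdrawn on changes of 2 or 3 points follows exactly from the text. The harm is avoidable loss of sessions and week 6 outcomes, and of the week 3 MADRS when the trigger comes at week 1 or 2. Its frequency is unknown; every probability above rests on assumed rating error, independent visits and an assumed true score. This is a change worth considering, not a threat to the trial's validity. Confidence is highest for the MADRS clause. For the YMRS, the balance between false triggers and missed manic worsening is for the investigators to judge.

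**What to change.** 1. **MADRS (main change).** Keep the 25% limit, but apply no trigger while the current score is below 11. Nothing changes at current scores of 11 or more, and the safety cost is very small because the patient is still in remission.

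2. **YMRS (only as a pair).** Withdraw on a rise above 50% and of at least a stated number of points, for example 5, to be set clinically, over either the previous week or baseline. When the previous score is 0, the point minimum alone applies. Baseline is at least 3, so the baseline percentage is always defined. Do not adopt the minimum without the baseline test.

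The cost is a short amendment, with no new assessments. The week-on-week minimum changes nothing when the previous YMRS is 8 or more, because the 50% limit already needs 5 points there. Two downsides remain. Some low-score rises, such as 3 to 7, are acted on up to one visit later, or not under this criterion if they stop short of the minimum. The baseline test also adds a few false triggers at higher scores (3.3% to 4.4% at true YMRS 15, SD 2).

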## Discussion

Here we provided the study protocol of a randomized controlled trial (RCT) that will evaluate the efficacy of TBS for the treatment of mixed depression of both bipolar and unipolar disorders. To the best of our knowledge, this is the first study in this field. Will be applied 21 sessions of bilateral TBS, comprising first inhibitory stimulation delivered by cTBS in the right DLPFC followed by excitatory stimulation delivered by iTBS in the left DLPFC, totalizing 3600 pulses. We performed sample size calculation based on the effect size found in the most similar clinical trial found in literature (41). The CANMAT guidelines provide the first- and second-line adequate treatments to treat both unipolar and bipolar depression (55). So far, there is no scientific recommendations to treat mixed depression. So that, we will include patients in a regular use (at least 30 days) of a first or second-line treatment of a CANMAT treatment and still presents with a moderate or severe major depressive episode. Patients with different drug treatments will be included, which will significantly increase the external validity of the results (73).

Previous studies indicate that mixed features population have distinct clinical and treatment response characteristics and has been associated with higher comorbidities, higher relapse rates, worse clinical outcomes, and higher suicide risk (51, 74, 75). We defined the MADRS (48) to assess depression symptoms and YMRS (49) to assess maniac symptoms. While some studies defined mixed depression considering YMRS ≥ 4 points (51, 74), recent data suggests that YMRS with ≥ 1 point on three or more items according are appropriate to classify this issue (12). Although any RCT with TBS has been performed so far in mixed depression, one clinical trial evaluated the efficacy of bilateral TBS in refractory non-mixed depression (41). Our RCT differs from this one in several ways, including a larger sample size (90 vs. 60) and comprising mixed depression presentation of both BD and MDD. In addition to the primary outcome that will assess the efficacy of TBS in mixed depression, this study will evaluate the effect of this technique on anxious symptoms, impulsivity, biological rhythms, functionality, quality of life, and cognition, the latter through a computerized neuropsychological battery.

We are aware that our study has some limitations. The current study will be an add-on TBS study, in spite of the randomized and sham-controlled design. It has been reported that add-on repetitive TMS treatment could enhance the clinical responses to antidepressants (76), therefore, the observed responses to TBS could partly result from modulation of the effects of the medications that patients were using during the TBS treatment. However, before we have solid evidence to support the antidepressant efficacy of TBS, the add-on design is more ethically sounded and could provide more real-life data. The concomitant medications will not be allowed to be changed and will be their original medication regimen which they had failed to respond to. Someone could consider mixed sample (BDI, BDII and unipolar depression) a limitations of the study, however last decade evidence corroborated the change that occurred in the DSM-5 in which the old mood episode called “mixed state” (only allowed in bipolar I disorder) was removed and changed into a mood specifier that can be applied to major depressive episodes of both bipolar I disorder, bipolar II disorder, and MDD (unipolar depression). This change suggests that the major depressive episodes of these diseases are similar in terms of clinical presentation, so much that the specifier “with mixed features” (mixed depression) can be attributed to all of them. The fact that these are different diseases might not affect the treatment of the acute depressive episode, similar to what we observe in antidepressants use to treat acute depression of MDD, bipolar II disorder and even bipolar I disorder (protected by mood stabilizers) (55). Thus, consolidating a recent transdiagnostic approach to psychiatric diseases, our objective is also to verify whether the same clinical presentation (mixed depression) could be treated in the same way with TBS regardless of the diagnosis, since all patients will be in a moderate or severe mixed depression.

